4.0 will be utilized for AE reporting. All appropriate treatment areas should have access to a copy of the CTCAE version 4.0. A copy of the CTCAE version 4.0 can be downloaded from the CTEP web site: (<http://ctep.cancer.gov/protocolDevelopment/electronic_applications/ctc.htm>)

1. Identify the grade and severity of the event using the CTCAE version 4.0.
2. Determine whether the event is expected or unexpected (see Section 10.2).
3. Determine if the adverse event is related to the study intervention (agent, treatment or procedure) (see Section 10.3).
4. Determine whether the event must be reported as an expedited report. If yes, determine the timeframe/mechanism (see Section 10.4).
5. Determine if other reporting is required (see Section 10.5).
6. Note: All AEs reported via expedited mechanisms must also be reported via the routine data reporting mechanisms defined by the protocol (see Sections 10.6 and 18.0).

NOTE: A severe AE is NOT the same as a serious AE, which is defined in Section 10.4.

- 1. Expected vs. Unexpected Events

*Expected events* - are those described within the Section 15.0 of the protocol, the study specific consent form, package insert (if applicable), and/or the investigator brochure, (if an investigator brochure is not required, otherwise described in the general investigational plan).

*Unexpected adverse events* or suspected adverse reactions are those not listed in Section

15.0 of the protocol, the study specific consent form, package insert (if applicable), or in the investigator brochure (or are not listed at the specificity or severity that has been observed); if an investigator brochure is not required or available, is not consistent with the risk information described in the general investigational plan.

*Unexpected* also refers to adverse events or suspected adverse reactions that are mentioned in the investigator brochure as occurring with a class of drugs but have not been observed with the drug under investigation.

An investigational agent/intervention might exacerbate the expected AEs associated with a commercial agent. Therefore, if an expected AE (for the commercial agent) occurs with a higher degree of severity or specificity, expedited reporting is required.

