**Grade 3 “Pregnancy, puerperium and perinatal conditions**

**- Other (pregnancy)”** under the Pregnancy, puerperium and perinatal conditions SOC. Pregnancy should be followed until the outcome is known.

10.562 Fetal Death

Fetal death is defined in CTCAE as “A disorder characterized by death in utero; failure of the product of conception to show evidence of respiration, heartbeat, or definite movement of a voluntary muscle after expulsion from the uterus, without possibility of resuscitation.”

Any fetal death should be reported expeditiously, as **Grade 4 “Pregnancy, puerperium and perinatal conditions - Other (pregnancy loss)”** under the Pregnancy, puerperium and perinatal conditions SOC.

10.563 Death Neonatal

Neonatal death, defined in CTCAE as “A disorder characterized by cessation of life occurring during the first 28 days of life” that is felt by the investigator to be at least possibly due to the investigational agent/intervention, should be reported expeditiously.

A neonatal death should be reported expeditiously as **Grade 4 “General disorders and administration - Other (neonatal loss)”** under the General disorders and administration SOC.

- 1. Required Routine Reporting
  2. Baseline and Adverse Events Evaluations

Pretreatment symptoms/conditions to be graded at baseline and adverse events to be graded at each evaluation.

Grading is per CTCAE v4.0 **unless** alternate grading is indicated in the table below:

| System Organ Class (SOC) | Adverse event/Symptoms | Baseline | Each evaluation |
| --- | --- | --- | --- |
| Blood and lymphatic system disorders | Anemia | X | X |
| Gastrointestinal disorders | Baseline # stools | X |  |
|  | Diarrhea |  | X |
| General disorders | Fatigue | X | X |
|  | Fever |  | X |
| Immune system disorders | Allergic reaction |  | X |
|  | Anaphylaxis |  | X |
| Investigations | Blood bilirubin increased |  | X |
| Respiratory system disorders | Dyspnea | X | X |

| System Organ Class (SOC) | Adverse event/Symptoms | Baseline | Each evaluation |
| --- | --- | --- | --- |
| Skin and subcutaneous tissue disorders | Rash, maculo-papular | X | X |

- 1. Other AEs

Submit via appropriate MCCC Case Report Forms (i.e., paper or electronic, as applicable) the following AEs experienced by a patient and not specified in Section 10.6:

10.621 Grade 2 AEs deemed *possibly, probably, or definitely*

related to the study treatment or procedure.

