10.622 Grade 3 and 4 AEs regardless of attribution to the study treatment or procedure.

10.623 Grade 5 AEs (Deaths)

10.6231 Any death within 30 days of the patient’s last study treatment or procedure regardless of attribution to the study treatment or procedure.

10.6232 Any death more than 30 days after the patient’s last study treatment or procedure that is felt to be at least possibly treatment related must also be submitted as a Grade 5 AE, with a CTCAE type and attribution assigned.

- 1. Late Occurring Adverse Events

Refer to the instructions in the Forms Packet (or electronic data entry screens, as applicable) regarding the submission of late occurring AEs following completion of the Active Monitoring Phase (i.e., compliance with Test Schedule in Section 4.0)

- 1. Pharmacyclics Additional Event Reporting Instructions Definitions

Adverse Events

An AE is any untoward medical occurrence in a subject administered a pharmaceutical product and which does not necessarily have a causal relationship with this treatment. An AE can therefore be any unfavorable and unintended sign (including a clinically significant abnormal laboratory finding, for example), symptom, or disease temporally associated with the use of an investigational study drug, whether or not considered related to the study drug (ICH-E2A 1995).

For the purposes of this clinical study, AEs include events which are either new or represent detectable exacerbations of pre-existing conditions.

The term “disease progression” should not be reported as an AE term. As an example, "worsening of underlying disease" or the clinical diagnosis that is associated with disease progression should be reported.

Adverse events may include, but are not limited to:

- - - Subjective or objective symptoms provided by the subject and/or observed by the investigator or study staff including laboratory abnormalities of clinical significance.
    - Any AEs experienced by the subject through the completion of final study procedures.
    - AEs not previously observed in the subject that emerge during the protocol- specified AE reporting period, including signs or symptoms associated with the underlying disease that were not present before the AE reporting period
    - Complications that occur as a result of protocol-mandated interventions (eg, invasive procedures such as biopsies).

The following are NOT considered AEs:

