    - Dose Expansion Cohort: The endpoint is tumor response. Patients will be classified with respect to their best tumor response during treatment (e.g., CR, PR, SD, confirmed PD, Death, Too Early, or Not Evaluable). Estimates of tumor response and binomial confidence intervals will be reported. A patient whose tumor has meet the RECIST criteria for CR or PR on two consecutive evaluations at least 8 weeks apart is considered to have had a tumor response.

Adverse events: The maximum grade of each type of toxicity will be recorded for each patient. For each toxicity reported by dose level, the percentage of patients developing any degree of that toxicity as well as the percentage of patients developing a severe degree (Grade 3 or higher) will be determined.

Secondary end points include tumor response (for the Phase I/Dose Seeking Cohort), progression-free survival (PFS) and overall survival (OS) time: A patient whose tumor has meet the RECIST criteria for CR or PR on two consecutive evaluations at least 8 weeks apart is considered to have had a tumor response. Survival time is defined as the time from study entry to death due to any cause. Progression-free survival time is the time from study entry to the documentation of disease progression. If a patient dies

without a recurrence documented, the patient will be considered to have progressed on their death date.

All the study observations pertaining to adverse events, MTD, response, time to event points and laboratory correlates will be examined in an exploratory and hypothesis- generating fashion. The small sample size and the heterogeneous patient population associated with Phase I studies restricts the generalizability of the results. Any notable statistical finding will be viewed as an impetus for further study in Phase II trials rather than a definitive finding in and of itself.

- 1. Monitoring of the trial

This clinical trial will be monitored by the Mayo Clinic Cancer Center Data and Safety Monitoring Board (MCCC DSMB). The study statistician will prepare a report containing accrual and adverse event that will be submitted to MCCC DSMB every 3 months.

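### Section 16.6 reports an any-degree percentage for each toxicity, but low-grade events outside nine solicited terms are not routinely collected, so those percentages are biased downward

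*Protocol*

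**What the plan says.** **Analysis.** Protocol Section 16.6 (Definition of end points and analysis plan, paragraph on adverse events) states: "The maximum grade of each type of toxicity will be recorded for each patient". For each toxicity reported by dose level it then calls for "the percentage of patients developing any degree of that toxicity as well as the percentage of patients developing a severe degree", where severe means Grade 3 or higher. It sets no lower grade limit and no attribution filter.

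**Collection, solicited terms.** Section 10.6 (Required Routine Reporting) opens its table with "Pretreatment symptoms/conditions to be graded at baseline and adverse events to be graded at each evaluation". Nine terms are marked for each evaluation: anemia, diarrhea, fatigue, fever, allergic reaction, anaphylaxis, blood bilirubin increased, dyspnea and maculo-papular rash.

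**Collection, everything else.** The next subsection (Other AEs) asks sites to submit "the following AEs experienced by a patient and not specified in Section 10.6". Three categories follow: Grade 2 events judged at least possibly related (10.621); "Grade 3 and 4 AEs regardless of attribution to the study treatment or procedure" (10.622); and Grade 5 events (10.623).

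**Link from expedited to routine data.** Section 10.1 adds: "All AEs reported via expedited mechanisms must also be reported via the routine data reporting mechanisms defined by the protocol".

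**The concern.** The analysis text presumes all-grade data on every toxicity, while the collection text provides all-grade data on nine terms only. Under a single any-degree heading, the table would mix full counts for those nine with counts for other terms that are cut off by grade and filtered by attribution. A reader has no means of telling the two apart.

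The adverse-event profile of the combination is the first secondary goal in Section 2, and Section 16 says the additional patients at the maximum tolerated dose are enrolled partly for insight into safety. Several common effects of the two drugs are not on the solicited list. Nausea, cough, constipation, vomiting and headache are frequent in the ibrutinib pool of Appendix VI. Pruritus is given in Section 1 as a 26% any-grade drug-related event with pembrolizumab. For such terms the combination could look milder at low grades than it is.

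**Working it through.** The plan states no figure to reproduce here. The check compares the analysis and collection texts, then bounds the size of the gap with the protocol's own data.

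**Step 1. What reaches the routine forms**

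| Event | Nine solicited terms | All other terms |
|---|---|---|
| Grade 1 | graded at each evaluation | no line asks for it |
| Grade 2, not related | graded at each evaluation | no line asks for it |
| Grade 2, at least possibly related | graded at each evaluation | submitted (10.621) |
| Grade 3 and 4 | graded at each evaluation | submitted, any attribution (10.622) |
| Grade 5 | submitted | submitted (10.623; deaths beyond 30 days if at least possibly related) |

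For the right-hand column, the any-degree numerator omits two kinds of event and adds none. The error can only be downward. The Grade 3+ numerator does not depend on the missing rows.

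**Step 2. Other routes for low-grade events**

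- The expedited reporting table in Section 10.4 takes Grade 1 and 2 events with hospitalization of 24 hours or more, and Section 10.1 sends expedited events to the routine data as well.
- The major hemorrhage definition takes central nervous system bleeding of any grade and serious bleeding of any grade.
- The subsection on other malignancies requires every new malignancy to be entered on the electronic form.

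These are real routes, but none covers an ordinary outpatient Grade 1 nausea, cough or pruritus.

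**Step 3. How common low-grade events are.** Inputs are counts from Appendix VI (ibrutinib pool, N = 1741) for terms not on the solicited list. The share below Grade 3 is (all grades − Grade 3+) / all grades.

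| Term | All grades | Grade 3+ | Below Grade 3 | Share |
|---|---|---|---|---|
| Nausea | 467 (26.8%) | 11 (0.6%) | 456 | 97.6% |
| Cough | 345 (19.8%) | 2 (0.1%) | 343 | 99.4% |
| Constipation | 276 (15.9%) | 4 (0.2%) | 272 | 98.6% |
| Vomiting | 252 (14.5%) | 10 (0.6%) | 242 | 96.0% |
| Headache | 229 (13.2%) | 12 (0.7%) | 217 | 94.8% |

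**Step 4. Range of the reported figure.** Appendix VI gives neither the split between Grade 1 and Grade 2 nor attribution. Let s be the assumed share of the below-Grade-3 patients who are not captured. For nausea the reported any-degree rate is (467 − s × 456) / 1741:

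| s | Calculation | Rate |
|---|---|---|
| 0 | 467 / 1741 | 26.8% |
| 0.25 | 353 / 1741 | 20.3% |
| 0.50 | 239 / 1741 | 13.7% |
| 0.75 | 125 / 1741 | 7.2% |
| 1 | 11 / 1741 | 0.6% |

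Section 16 caps enrollment at the maximum tolerated dose at 16 patients. There the expected number with nausea would be 16 × 0.268 = 4.3 at one end and 16 × 0.0063 = 0.1 at the other.

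**The case against.** **The sentence is limited to toxicities reported.** On this reading any degree means any reported degree, and no complete incidence was promised. The qualifier narrows which rows appear, but it does not make the column heading true. The preceding sentence, on recording the maximum grade of each type, carries no such limit.

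**Low-grade events do reach the database.** A reader might infer that Grade 1 and unrelated Grade 2 events are never submitted. The documents do not support that, given the routes in Step 2. The list of exceptions to expedited reporting (Section 10.32) also includes nausea, vomiting, arthralgia and myalgia up to Grade 3 and says they must still be reported routinely. That list is headed as expected serious events and refers back to Section 10.6, so whether it widens routine collection is arguable. The Forms Packet and the Data Submission Schedule, to which the protocol refers, are not at hand. What stands is that these events are not routinely requested.

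**The size is unknown.** A reader might take the whole gap between 26.8% and 0.6% as lost. That is also unsupported: related Grade 2 events are collected, and possible relation is enough. Only a range can be given.

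**Little depends on it.** Section 16.6 calls the analyses exploratory, and no formal comparison with Appendix VI is planned. Rash, which prompted the redesign, is solicited. The graded triggers in the stopping rules (16.71) concern related events and start at Grade 2, and the study team monitors dose-limiting toxicities directly. All of this stands and limits the consequence to the safety summary. An exploratory percentage still needs a correct label.

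**Labels belong in an analysis plan.** Often so. Here the protocol itself fixes the summary and the collection rule, the two disagree, and a later plan cannot recover events that were not submitted.

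**Conclusion.** The point holds in a limited form. For terms outside the nine solicited ones, the any-degree percentage of Section 16.6 will rest on truncated, attribution-filtered data. It is biased downward by an amount the protocol does not determine. With the illustrative Appendix VI rates, nausea would read between 26.8% and 0.6%. That range assumes that this trial's patients resemble the ibrutinib pool, and it leaves the grade split and attribution open. Grades for laboratory terms might be derived from the scheduled blood counts and chemistry, but the protocol does not say so.

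The Grade 3+ percentages, the nine solicited terms, dose-limiting toxicities, the maximum tolerated dose, the stopping rules and the response rule are not affected. The change should be made, because it prevents a misleading table for a stated secondary goal at almost no cost.

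**What to change.** In Section 16.6, limit any-degree percentages to the nine terms graded at each evaluation under Section 10.6. For every other term, report the Grade 3+ percentage and a second column labelled *events collected under Section 10 (routinely: related Grade 2 or any Grade 3+)*. That wording allows for the hospitalized, bleeding and malignancy events that enter by other routes. A bare label of related Grade 2 or Grade 3+ would be wrong for those rows.

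The cost is one sentence and the table labels, with no new data collection. The downside is that unsolicited terms have no any-grade figure. The alternative is to collect all grades of all terms regardless of attribution. That would give such figures, but it adds work for sites and would leave data from patients already treated incomplete unless collected retrospectively.

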16.71 Safety Stopping rules

Dose limiting toxicities and other acute adverse events will be monitored by the study team on a monthly basis. If during the course of enrolling the first 6 patients on trial, 2 patients develop a grade 3+ maculo-papular rash, pneumonitis, nephritis, fever, allergic reaction, anaphylaxis, dyspnea, or increased blood bilirubin or grade 4 hyperthyroidism, hypophysitis or diarrhea, which are considered possibly, probably, or definitely related to treatment, any time during treatment enrollment will be temporarily closed.

Any time after the first 6 patients have been enrolled, if 30% or more of the patient enrolled develop one (or more) of the toxicities listed in the table below during treatment or within 30 days of discontinuing protocol treatment and the toxicity is considered to be possibly, probably, or definitely related to treatment, enrollment will be temporarily closed.

| **Toxicity** | **Severity/duration** |
| --- | --- |
| Neurologic | Grade 2 and not resolved to ≤ Grade 1 within 14 days  ≥ Grade 3 regardless of time to resolution |
| Hematologic | Grade 4 and not resolved to ≤ Grade 1 within 14 days  Grade 3 with Grade 3+ febrile neutropenia or hemorrhage, regardless of time to resolution |
| Other | Grade 3 and not resolved to ≤ Grade 1 within 14 days  Grade 4 regardless of time to resolution  Any toxicity that leads to treatment discontinuation due to toxicity |

- 1. Inclusion of Women and Minorities

| **Accrual Targets** | | | |
| --- | --- | --- | --- |
| **Ethnic Category** | **Sex/Gender** | | |
|  | **Females** | **Males** | **Total** |
| Hispanic or Latino | 0 | 1 | 1 |
| Not Hispanic or Latino | 10 | 12 | 22 |
| **Ethnic Category: Total of all subjects*** | **10** | **13** | **23** |
| **Racial Category** | | | |
| American Indian or Alaskan Native |  |  |  |
| Asian |  |  |  |
| Black or African American |  |  |  |
| Native Hawaiian or other Pacific Islander |  |  |  |
| White | 10 | 13 | 23 |
| **Racial Category: Total of all subjects*** | **10** | **13** | **23** |

| **Ethnic Categories:** | **Hispanic or Latino –** a person of Cuban, Mexican, Puerto Rican, South or Central American, or other Spanish culture or origin, regardless of race. The term “Spanish origin” can also be used in addition to “Hispanic or Latino.”  **Not Hispanic or Latino** |
| --- | --- |
| **Racial Categories:** | **American Indian or Alaskan Native –** a person having origins in any of the original peoples of North, Central, or South America, and who maintains tribal affiliations or community attachment.  **Asian –** a person having origins in any of the original peoples of the Far East, Southeast Asia, or the Indian subcontinent including, for example, Cambodia, China, India, Japan, Korea, Malaysia, Pakistan, the Philippine Islands, Thailand, and Vietnam. (Note: Individuals from the Philippine Islands have been recorded as Pacific Islanders in previous data collection strategies.)  **Black or African American –** a person having origins in any of the black racial groups of Africa.  **Native Hawaiian or other Pacific Islander –** a person having origins in any of the original peoples of Hawaii, Guam, Samoa, or other Pacific Islands.  **White –** a person having origins in any of the original peoples of Europe, the Middle East, or North Africa. |

MC1577 66 MCCC Amendment 8

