***ALERT:* ADR reporting may be required for some adverse events (See Section 10)**

- 1. Dose Levels

(Based on Adverse Events in Table 8.2)

| **Dose Level** | **Ibrutinib** | **Pembrolizumab** |
| --- | --- | --- |
| 1* | 420 mg PO once daily | 200 mg IV |
| -1 | 280 mg PO once daily | NA |
| -2 | 140 mg PO once daily | NA |

*Dose level 1 refers to the starting dose.

- 1. Dose Modifications Based on Adverse Events

NOTE: These modifications only apply if the adverse event is **possibly**, **probably**, or

**definitely** related to study treatment

| **System/Organ/Class (SOC)** | **ADVERSE EVENTS/SYMPTOMS** | **ACTIONS** | |
| --- | --- | --- | --- |
|  |  | **Pembrolizumab** | **Ibrutinib** |
| Blood and lymphatic | **Anemia** | | |
| system disorders | Grade 4 | Hold pembrolizumab until  ≤Grade 2 and etiology is  determined  If anemia is immune-mediated (at least possibly related to pembrolizumab), discontinue pembrolizumab | Discontinue ibrutinib |
|  | **Febrile neutropenia (See also Investigations/Neutrophil count decreased)** | | |
|  | Grade 3 | Hold until symptoms resolve to  ≤Grade 1 | Hold until symptoms resolve to  ≤Grade 1;  Resume at the next lower dose level (if occurs at 140 mg once daily, discontinue) |
|  | Grade 4 | Hold until symptoms resolve to  ≤Grade 1 | Discontinue ibrutinib |
| Cardiac disorders | **Cardiac arrythmias** | | |
|  | Grade 3 | Continue pembrolizumab | Hold until symptoms resolve to  ≤Grade 1, then resume Resume at the next lower dose level  (if occurs at 280 mg once daily or lower, discontinue ibrutinib) |
|  | Grade 4 | Discontinue and enter Event Monitoring. | Discontinue and enter Event Monitoring |

| **System/Organ/Class (SOC)** | **ADVERSE EVENTS/SYMPTOMS** | **ACTIONS** | |
| --- | --- | --- | --- |
|  |  | **Pembrolizumab** | **Ibrutinib** |
| Cardiac disorders | **Cardiac failure** (not due to immune-related myocarditis) | | |
|  | Grade 2 | Hold until symptoms resolve to  ≤Grade 1, then resume | Hold until symptoms resolve to  ≤Grade 1;  Resume at the next lower dose level (if occurs at 140 mg once  daily, discontinue) |
|  | Grade 3 or 4 | Discontinue and enter Event Monitoring. | Discontinue and enter Event Monitoring. |
| Cardiac disorders | **Myocarditis** | | |
|  | Grade 2+ | Discontinue and enter Event Monitoring. | Discontinue and enter Event Monitoring. |
| Endocrine Disorders | **Symptomatic Hypophysitis** | | |

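### Section 16.71 closure table: a Grade 4 cytopenia with febrile neutropenia or hemorrhage that resolves within 14 days may go uncounted, while the same event at Grade 3 counts

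*Protocol*

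**What the plan says.** Section 16.71 of the protocol has a second closure rule, applying at any time after the first 6 patients are enrolled. Enrolment closes temporarily "if 30% or more of the patient enrolled develop one (or more) of the toxicities listed in the table below", if the event is possibly, probably or definitely related and occurs "during treatment or within 30 days of discontinuing protocol treatment".

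The table's lines are:

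- **Neurologic:** Grade 2 not resolved to Grade 1 or less within 14 days, and "≥ Grade 3 regardless of time to resolution".
- **Hematologic:** "Grade 4 and not resolved to ≤ Grade 1 within 14 days", and "Grade 3 with Grade 3+ febrile neutropenia or hemorrhage, regardless of time to resolution".
- **Other:** Grade 3 not resolved to Grade 1 or less within 14 days; "Grade 4 regardless of time to resolution"; and "Any toxicity that leads to treatment discontinuation due to toxicity".

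Table 8.2 in Section 8 bears on the last of these lines. For Grade 3 febrile neutropenia both drugs are held, and the ibrutinib instruction is "Resume at the next lower dose level (if occurs at 140 mg once daily, discontinue"). The rows for Grade 4 neutropenia and for low platelets likewise hold both drugs and allow them to resume.

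**The concern.** A toxicity count that can pause enrolment should not lose an event because the event is more severe. In the hematologic row, moving from a Grade 3 to a Grade 4 cytopenia, with the complication unchanged, adds a condition: the event must persist beyond 14 days. The table marks open-ended grades elsewhere, with the sign in the Neurologic row and the plus inside the disputed line itself. The bare grade can therefore be applied literally by whoever tallies the events.

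The same feature leaves Grade 5 unnamed outside the Neurologic row, although Section 10.623 treats deaths as Grade 5 adverse events.

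At stake is only which events count toward a temporary closure of enrolment. In a trial of at most 23 patients, that decision turns on a handful of events.

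**Working it through.** The protocol gives no operating characteristic for the 30% rule, so there is no figure to reproduce. The check has three parts.

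**1. Each line applied literally to example events, all assumed treatment-related**

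| Event | Counted? | Why |
| --- | --- | --- |
| Grade 3 cytopenia with Grade 3 febrile neutropenia, resolved within 14 days | Yes | Second hematologic line |
| Grade 4 cytopenia with Grade 3 febrile neutropenia, resolved within 14 days, treatment resumed | No | First line needs persistence; second names Grade 3 |
| Same Grade 4 event, unresolved at 14 days | Yes | First hematologic line |
| Grade 5 neurologic | Yes | Line is open-ended upward |
| Grade 5 other, on treatment | Arguably | Only if death is read as discontinuation due to toxicity |
| Grade 5 non-neurologic, within 30 days of stopping for another reason | Not clearly | No line outside Neurologic names Grade 5, and the toxicity did not cause the stop |

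The first two rows show that the table is not monotone in severity.

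**2. Does the discontinuation line close the gap?**

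Table 8.2 gives these actions:

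- Grade 4 neutropenia, platelets below 25 x 10^9/L, or platelets below 50 x 10^9/L with clinically significant bleeding: both drugs are held and may resume. Ibrutinib is discontinued if the event occurs at 140 mg; pembrolizumab is discontinued if recovery to Grade 2 or less takes more than 12 weeks from the last dose.
- Grade 3 febrile neutropenia: both drugs are held; ibrutinib resumes at a lower level unless already at 140 mg.
- Grade 4 febrile neutropenia and Grade 4 anemia: ibrutinib is discontinued and pembrolizumab is held. It is discontinued only for immune-mediated anemia.

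For the first two groups, a patient can recover and resume without meeting the discontinuation line. For the third, the answer depends on whether stopping one drug is treatment discontinuation, which Section 16.71 does not say.

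**3. How small are the counts?**

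The number needed at n patients is 0.30 × n, rounded up. The rule starts at n = 7.

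| Patients enrolled | 0.30 × n | Events to close |
| --- | --- | --- |
| 7-10 | 2.1-3.0 | 3 |
| 11-13 | 3.3-3.9 | 4 |
| 14-16 | 4.2-4.8 | 5 |
| 17-20 | 5.1-6.0 | 6 |
| 21-22 | 6.3-6.6 | 7 |

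The table stops at 22 because Section 16 (Sample Size) caps enrolment at 23; at the 23rd patient there is nothing left to close.

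As an illustration, take independent patients, a look after each from the 7th to the 22nd, and each event known at once. Updating the binomial count patient by patient and removing paths that reach the threshold gives the chance of ever closing. The true rates and the percentage points lost are assumptions, not protocol figures.

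| True rate | All counted | 1 point lost | 2 points lost | 5 points lost |
| --- | --- | --- | --- | --- |
| 30% | 75% | 72% | 69% | 59% |
| 40% | 94% | 93% | 91% | 86% |

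A loss of 1 or 2 points moves the chance of closure by about 1 to 6 percentage points. The 5-point column is an outer bound: all Grade 3 or higher febrile neutropenia in the Appendix VI ibrutinib pool is 80/1741 = 4.6%, and only part of that could escape the table.

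**The case against.** Much of the table does catch severe events.

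- **Bleeding.** The list in Section 10 of events exempt from expedited reporting places gastric, bronchopulmonary and intracranial hemorrhage outside the blood system. On that classification a Grade 4 bleed counts in the Other row, and an intracranial bleed treated as neurologic counts from Grade 3. Only a Grade 3 non-neurologic bleed that resolves within 14 days without discontinuation escapes on its own account. This stands, and leaves febrile neutropenia as the main route for a missed event.
- **The worst hematologic events.** Grade 4 febrile neutropenia and Grade 4 anemia lead to ibrutinib being stopped, so they are plausibly counted. This stands if stopping one drug qualifies.
- **Deaths.** Neurologic Grade 5 events count, and most on-treatment toxic deaths would count as discontinuation due to toxicity. A fatal event may also have met a listed line before death. Section 10 (Death) requires 24-hour reporting of any death within 30 days of the last dose. That reporting is useful, but does not decide what enters the 30% count.
- **Intent.** A sensible study team would probably read the Grade 3 line as Grade 3 or higher. That is likely, but the table uses explicit open-ended notation elsewhere.

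A reader might infer that the rule misses the most serious toxicities in general, or that it is the trial's only monitoring of late toxicity. The documents support neither. Section 16.71 has another rule, for the first 6 patients, covering listed events at any time during treatment. The study team reviews toxicity monthly, and the DSMB receives adverse-event reports every 3 months. The expansion-cohort checks after 3 and 6 patients use a DLT definition that counts Grade 4 ANC or hemoglobin with no duration condition, though only for the first cycle.

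Nor should the pool's 4.6%, about 1 patient in 23 (23 × 0.046 = 1.06), be read as the expected number missed. It is a ceiling on febrile neutropenia cases, from a different disease. A missed case must also accompany a Grade 4 cytopenia, be related, resolve within 14 days, not end treatment and meet no other line.

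**Conclusion.** The point holds as a wording defect. The hematologic row is not monotone in severity, and the discontinuation line does not reliably repair it because Table 8.2 lets treatment resume after the events concerned. The Grade 5 gap is real but narrower: related non-neurologic deaths within 30 days of stopping for another reason.

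The likely effect is small. Few events would meet all the conditions for being missed, and a missed event changes the decision only when the count is exactly one short. It is still worth correcting because the thresholds are only 3 to 7 events. The conclusion rests on a literal reading of the table; if the study team already counts Grade 3 or higher, the text only needs to say so. The closure probabilities rest on assumed rates and show scale only.

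**What to change.** In the Section 16.71 table:

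1. Change the second hematologic line from Grade 3 to Grade 3 or higher, leaving the febrile neutropenia or hemorrhage condition as it is.
2. Name Grade 5 in the Hematologic and Other rows.

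With these changes every example event in the working counts, and the numbers needed for closure stay the same. The cost is a few words in one table at the next amendment. Only the tally for temporary enrolment closure changes; dosing and patient management under Section 8 are not touched. The team should also check any events already tallied against the corrected wording.
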